# Early childhood intervention for children at risk of developmental disabilities and their caregivers in Rwanda: study protocol for the PDC/Baby Ubuntu cluster randomised trial

**DOI:** 10.1186/s13063-026-09613-7

**Published:** 2026-03-20

**Keywords:** Disability, Child, Caregiver, Participation, Quality of life, Randomised controlled trial, Process evaluation

## Abstract

**Background:**

Early childhood intervention strategies have the potential to promote health, participation and quality of life for young children at risk of developmental disabilities and their caregivers, however evidence on the impact of integrated care strategies in sub-Saharan Africa is lacking. Access to early intervention is crucial for affected children and families, particularly in resource-constrained settings with limited access to specialised services. This trial aims to evaluate the effectiveness and implementation of a bundle of early identification, care and support, integrated into government health systems in Rwanda: the Pediatric Development Clinic (PDC)/Baby Ubuntu programme.

**Methods:**

The study is a single-blind, effectiveness implementation-hybrid (type II) cluster randomised controlled trial with two arms (1:1 ratio). At cluster level, all community health centres in the three trial districts will be eligible for inclusion. At the participant level, at risk children aged ≤ 59 months will be eligible where ‘at risk’ is defined as being a survivor of a newborn condition that is a recognised risk factor for developmental disability (neonatal encephalopathy, prematurity, meningitis, severe jaundice, cerebral malaria, suspected genetic and chromosomal conditions and seizures), and/or not meeting age-specific developmental milestones. Those receiving inpatient hospital treatment or in institutional care will not be eligible. Primary outcomes will be family health-related quality of life (PedsQL) and child participation (Young Child Participation & Environment Measure) assessed 12 months after enrolment and randomisation. Secondary outcomes include caregiver knowledge and confidence (scored structured assessments), psychological distress (Self-Report Questionnaire), experience of disability-affiliated stigma (Affiliate Stigma Scale), and economic activity (time-use survey), in addition to child mortality, illness and hospitalisation, child development/function (Global Scales of Early Development, Malawi Developmental Assessment Tool, PEDI-CAT), and nutritional status (weight-for-age, height-for-age). Analysis will be by intention-to-treat, consisting of all randomised subjects analysed according to assigned study arm. Cluster-level analyses will assess intervention effect.

**Discussion:**

The trial utilises best practice methodology and frameworks to conduct rigorous and comprehensive impact, process and economic evaluation of the intervention implemented and is guided by a multi-disciplinary team and steering committee.

**Trial registration:**

ISRCTN, ISRCTN17523514. Retrospectively registered 24 July 2024, https://doi.org/10.1186/ISRCTN17523514

**Supplementary Information:**

The online version contains supplementary material available at 10.1186/s13063-026-09613-7.

## Background

Globally, more than 315 million children and young people are affected by health conditions that increase their risk of developmental disabilities [1]. In response, international policy increasingly advocates for attention on early child development and disability, especially in the first thousand days, a critical period for child development. Sustainable Development Goal target 4.2 aims to ensure all children have access to quality early childhood development and care, inclusive of young children with developmental disabilities [2]. Further, the *Nurturing Care Framework* provides a roadmap to meet the developmental needs of all children, although targeted and tiered support for those at risk of disabilities is clearly warranted [3]. Access to early intervention strategies for affected children and caregivers is crucial, however the majority live in low- and middle-income countries (LMICs) where access to specialised care may be limited [4]. Caregivers of children with developmental disabilities frequently experience stigmatisation, prejudice, institutionalisation and barriers to participation, that affect social, economic and health outcomes [1]. Whilst evidence-based interventions across the life course exist, there remains a critical evidence gap for effective, agile and integrated early intervention strategies for implementation in diverse global contexts.

Many common newborn conditions are associated with an increased risk of developmental disabilities. Whilst significant gains have been achieved in reducing neonatal mortality reduction worldwide [5], there has been less focus on longer-term morbidity and disability outcomes from conditions such as neonatal encephalopathy, prematurity and severe jaundice [6]. Delayed identification of developmental impairment and delay amongst high-risk infants can worsen long-term outcomes [7] and evidence, largely from high-income countries, suggests that care strategies that include early identification and intervention for at risk children may improve long-term child, caregiver and family outcomes [8]. Participatory approaches to promote caregiver knowledge and confidence can improve child participation and inclusion, both at home and in the community [9], and can support caregivers and families who experience stigma and discrimination, isolation and rising economic costs of caring [10, 11]. Early intervention programmes can promote access to care, create an improved caregiving environment and improve family quality of life [8, 9, 12], however, there is a paucity of data from LMICs [9, 13]. In addition, programmes are typically developed and implemented locally by non-governmental organisations, and almost all are targeted at older children (> 2 years) [9].

This cluster randomised controlled trial will evaluate the effectiveness and implementation of the Pediatric Development Clinic (PDC)/Baby Ubuntu programme, a bundle of early identification, care and support for young children (<5 years) at risk of developmental disabilities and their families, integrated with government health systems in Rwanda. The PDC provides targeted developmental monitoring and support for children at risk of developmental delay and disability due to perinatal risk factors, while Baby Ubuntu is a community-based, participatory, group programme of early care and expert parent peer support for children with developmental disabilities and their caregivers. The combined PDC/Baby Ubuntu programme aims to maximise caregiver and child quality of life and participation.

### Hypotheses, Aim and Objectives

#### Hypotheses

Primary effectiveness hypothesis: The PDC/Baby Ubuntu programme of early care and support for children at risk of developmental disabilities integrated into government health services in Rwanda is effective in improving family health-related quality of life and child participation, when compared to enhanced usual care.Primary implementation hypothesis: Integration of the PDC/Baby Ubuntu programme into government health systems at district level in Rwanda is feasible, acceptable and results in high-fidelity adoption, promoting reach of tier one services for children with developmental disabilities and their families.

#### Aim

This research aims to evaluate the effectiveness and implementation (feasibility, acceptability, cost, sustainability) of the PDC/Baby Ubuntu programme of early care and support for young children at risk of developmental disabilities and their caregivers integrated into government health systems in Rwanda.

#### Objectives

Specific objectives of the study are to:Evaluate the impact of the PDC/Baby Ubuntu programme on caregiver, family and child outcomes, including family health-related quality of life and child participation.Evaluate the feasibility and acceptability of PDC/Baby Ubuntu when integrated into government health systems at district level.Explore barriers and facilitators to sustainable implementation of the programme with fidelity when integrated into government health systems.Evaluate the cost and cost-effectiveness of the integrated programme.

## Methods

This protocol has been developed in line with SPIRIT (Standard Protocol Items: Recommendations for Interventional Trials) recommendations [14]. The completed SPIRIT checklist can be found in Supplementary Material 1. The trial was retrospectively registered on the ISRCTN registry (10.1186/ISRCTN17523514) prior to completion of participant enrolment. Retrospective registration occurred as a result of changes to Rwanda Law (No. 058/2021) that occurred during the trial inception period, which meant that approval from the Rwandan National Cyber Security Authority was required before details of the trial could be publicly shared.

The primary hypotheses will be tested through a single-blind, effectiveness implementation-hybrid (type II) cluster randomised controlled trial (cRCT) with two arms (1:1 ratio). Intervention clusters will receive the PDC/Baby Ubuntu programme, and control clusters enhanced usual care. For the main trial, trial outcome measures will be assessed in all clusters at two time points; baseline (T0) and endline, 12 months after enrolment and randomisation of the trial clusters (T1). Embedded process and economic evaluations will strengthen our understanding of programme implementation and scale-up. We will use the RE-AIM framework to guide the planning and evaluation of the programme according to five key outcomes: Reach, Effectiveness, Adoption, Implementation and Maintenance [15].

### Study setting

Rwanda ranks 160 out of 188 countries in the United Nations Development Program Human Development Index [16]. Child mortality has declined rapidly in Rwanda over the last few decades, with increased government investment in healthcare and expanding neonatal care facilities [17]. However, approximately 10% of newborns are born prematurely [18] and 24% of children are not achieving age-expected developmental milestones [17].

Rwanda operates a decentralised, tiered public health system, from primary care to national referral hospitals. At primary level, health centres deliver preventative, curative and promotional services. Health centres coordinate community health workers, who provide targeted support in local communities and connect households to primary healthcare. At secondary level, district hospitals provide diagnosis, treatment and inpatient care for patients referred from primary health centres. District hospitals coordinate primary health centres and organise district resources, logistics and health campaigns. Finally, at tertiary level, national referral hospitals deliver specialised care not available at district level. Standard care for all young children in Rwanda (including those at risk of developmental disabilities) includes home visits by community healthcare workers until age two, standard primary healthcare services at health centres and hospitals, child immunization, and referral to rehabilitation services at secondary and tertiary hospitals. There is no standard national package of care specifically for children at risk of developmental disabilities.

Three District Health Community Areas will be included in this trial: Burera, Gakenke, Kamonyi (Fig. 1). Burera is served by 19 health centres, Gakenke 23 health centres and Kamonyi 14 health centres. The unit of randomisation, a ‘cluster’, will be defined as the catchment area of two to three health centres in close geographic proximity. Each cluster will be surrounded by a buffer zone to limit contamination. In total, 20 clusters will be defined across the three districts; six clusters each in Kamonyi and Burera, eight clusters in Gakenke. In Supplementary Material 2 we have listed the health centres included in the trial and the total populations they serve.

**Fig. 1 Fig1:**
[figure not shown]
Map of Rwanda and Burera, Gakenke and Kamonyi districts

### Study participants

Eligibility criteria:

Eligible participants will be children at risk of developmental disabilities aged 0–5 years and their caregivers, where ‘at risk’ is defined as children with:History of a newborn condition that is a recognised risk factor for developmental disability: prematurity, neonatal infection, neonatal encephalopathy (‘birth asphyxia’), severe jaundice, cerebral malaria, suspected genetic and chromosomal conditions, and seizures [1, 19–21].Not meeting age-specific developmental milestones, identified through routine child health service contact points, such as immunisation clinics and health screening by community health workers.Positive screening for developmental disabilities on an adapted version of the Ten Question Questionnaire, a brief screening tool for childhood disability [22].

Inclusion criteria:Children (0–59 months) meeting the definition of ‘at risk’ and their caregivers.Living within the catchment area of one of the health centres in a study cluster.Caregiver is willing and able to give written informed consent to take part in the study.Caregiver is either 18 years of age or older or, if younger than 18 years and the biological parent of the child, they are considered emancipated youth and eligible for participation.

Children requiring hospital treatment and/or living in institutional care at the time of the baseline assessment will not be eligible.

### Screening and recruitment

Prospective eligible participants (at risk children) in the three districts will be identified at the start of the project through an established network of government community healthcare workers and electronic medical records. Prospective participants will be invited to their local health centre for screening. After verbal assent from the child’s caregiver, trained data collectors will administer a simple screening questionnaire to confirm that the child meets the inclusion criteria. Should the child be eligible, data collectors will invite the child’s primary caregiver (defined as the caregiver who spends the most time with the child) to participate in the study, taking written informed parental consent. Enrolment will be offered to caregivers of all eligible children. Enrolment will continue until the required sample size is reached in each district. Children will be enrolled at their local health centre (defined as the health centre they visit for care) as opposed to the health centre to which they are registered, which may be geographically further and not where they practically access care.

### Randomisation

After baseline assessment, the 20 clusters will be randomised using a 1:1 allocation ratio to either the intervention arm receiving the PDC/Baby Ubuntu programme or the control arm receiving enhanced usual care. Randomisation will be stratified by district. Restricted randomisation will be used to ensure balance on cluster size which was determined to be potentially prognostic of intervention outcomes. The characteristics included in the restriction (district, cluster size) will be adjusted for in the analysis. Allocation will be completed by the trial statistician, not otherwise involved in the conduct of the trial. The outcome assessment team will be blinded to the allocation status of trial participants.

### Participant timeline

Table 1 outlines the schedule of enrolment, interventions and assessments. Primary and secondary outcomes will be assessed at two timepoints: baseline (T0), and 12 months later after randomisation (T1).

**Table 1 Tab1:** Schedule of enrolment, assessment and intervention delivery

	Trial Period				
	Enrolment		Post-randomisation		Close-out
**Timepoint**	T0			T1	
**Enrolment**					
Eligibility screen	X				
Informed consent	X			X	
Baseline assessment	X				
Allocation		X			
**Intervention**					
Intervention arm			X	X	X
Control arm					X
**Assessment**					
Sociodemographic data	X				
Clinical characteristics	X				
Family health-related quality of life (PedsQL)	X			X	
Child participation (YC-PEM)	X			X	
Caregiver knowledge & confidence	X			X	
Caregiver psychological distress (SRQ)	X			X	
Caregiver experience of stigma (Affiliate Stigma Scale)	X			X	
Caregiver economic activity (time-use survey)	X			X	
Child survival (vital status)				X	
Child development (MDAT/GSED)	X			X	
Child function (PEDI-CAT)	X			X	
Child health (hospitalisations)				X	
Child anthropometric measurement (weight, height, OFC)	X			X	
**Process & economic evaluation**					
Qualitative data collection			X		
Economic data collection			X		

T0 = Baseline data collection; T1 = Endline data collection; YC-PEM = Young Children’s Participation and Environment Measure; PedsQL = Pediatric Quality of Life Inventory; MDAT = Malawi Development Assessment Tool; GSED = Global Scales for Early Development; PEDI-CAT = Pediatric Evaluation of Disability Inventory—Computer Adaptive Test; OFC = Occipital Frontal Circumference; SRQ = Self-Reporting Questionnaire

### Intervention description

The Pediatric Development Clinic (PDC) is an interdisciplinary model established in 2014 by Partners in Health/Inshuti mu Buzima (PIH/IMB) and the Rwanda Biomedical Centre (Ministry of Health) to monitor and provide targeted support within the public health system for children at risk of developmental delay and disability due to perinatal risk factors [23, 24]. Providers are non-specialised healthcare professionals, primarily general nurses and social workers. They are trained and mentored to deliver a structured package of neonatal follow-up and early intervention services based on components of nurturing care. Children enrolled in PDC are systematically followed up and are discharged from the programme at 36 months if they are developmentally on-track without any health or nutritional problems. PDCs implemented in Rwanda have demonstrated feasibility and improved child and caregiver outcomes [23, 24]. In a quasi-experimental study, post-neonatal unit mortality declined from 12 to 9% (p < 0.05), with a larger decline amongst preterm and low birth weight infants, reducing from 12.4% to 5.9% (p < 0.001).

Children attending the PDC who have severe developmental delay, assessed via the Guide for Monitoring Child Development (GMCD) [25], are referred to the Baby Ubuntu programme. Baby Ubuntu is a participatory, group-based, peer-led rehabilitation programme providing early care and support for young children with developmental disabilities and their caregivers. Group sessions are co-facilitated by community or facility-based healthcare professionals and ‘Expert Parents’, themselves parents of children with developmental disabilities. The content is divided into 11 modules, including information on understanding disability, positioning and carrying, feeding, communication, play, and experiences in the local community. Each session lasts for 2–3 hours. Evidence from mixed-methods, pre-post intervention evaluations of Baby Ubuntu in both urban and rural settings in Uganda have indicated a 20–25% increase in family and child health-related quality of life [26, 27]. A pilot feasibility, randomised-controlled trial in Uganda showed the programme to be both feasible and acceptable to families and health care workers in both rural and urban settings [28].

In 2019–20, the combined PDC/Baby Ubuntu bundle (Fig. 2) was piloted and evaluated in two rural districts of Rwanda integrated into government health systems [29]. Over three months, 10 PDCs enrolled 109 families to 12 Baby Ubuntu groups. Pre-post implementation evaluation showed a 20% increase in median family health-related quality of life score post intervention (62.5 vs. 79.9, p < 0.001). Significant improvements were seen in caregiver health-related quality of life and family functioning (p < 0.05). Satisfactory attendance was seen in 95% of families.

**Fig. 2 Fig2:**
[figure not shown]
The Pediatric Development Clinic/Baby Ubuntu bundle

For this trial, the combined PDC/Baby Ubuntu bundle will be delivered in intervention cluster health centres as part of routine government child health services. Recruited children in the intervention clusters will be invited to the PDC at the health centre at which they completed the baseline survey. Children identified as having a developmental disability will be invited to join the Baby Ubuntu programme.

### Enhanced usual care

Specialised services for children at risk of developmental disabilities are uncommon in Rwanda. Families are frequently dependent on routine child health services from which they may be excluded. Evidence-based interventions for early care and support for at risk children are not available in most health centres.

Enhanced usual care will be provided to all participants, including those in the comparison arm. Participants will be given a printed handout listing available services, facility address and contact details. In the comparison arm, children will receive’enhanced usual care’ alone. There will be no restriction on concomitant care.

### Baseline data

Child and caregiver demographic information will be recorded at baseline through standardised questionnaires. Demographic information for the child will include date of birth, age and sex. Caregiver demographics data will include name, age, gender, marital status, address, contact details, relationship with child, education, employment status and religion. We will collect information on the head of household (if not the caregiver,) including age, education and employment status. Information on family characteristics will also be collected, including family size, ages of household members, family residence, household assets and household Ubudehe category, an income category assigned to households in Rwanda by the government. Principal Component Analysis will be used to determine participant socioeconomic status.

Disability status at baseline will be determined using the Malawi Developmental Assessment Tool (MDAT), a developmental screening tool developed and validated for use in Sub-Saharan Africa [30]. The tool assesses culturally appropriate age-standardised developmental milestones across four domains: gross motor, fine motor, language and social. Items are scored as pass (1) or fail (0). The child’s score in each domain is defined as the number of items completed until failure in six consecutive items. Development-for-age Z-scores (DAZ) are calculated in the MDAT Scoring Application in Shiny version 1.1 (https://kieran-bromley.shinyapps.io/mdat_scoring_shiny). Moderate to severe developmental disability will be defined as DAZ scores < −2 on endline assessment when children are older and diagnosis are more reliable.

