### Effectiveness outcomes

Primary effectiveness outcomes are:*Family health-related quality of life*: measured using the caregiver self-reported Pediatric Quality of Life Family Impact module (PedsQL) [31]. The PedsQL assesses the impact of pediatric chronic health conditions (here developmental disability and associated at risk conditions) on caregiver physical, social, emotional, cognitive, wellbeing, communication and worry, as well as the impact on family activity and family relationships. Scores are categorised into total, caregiver health-related quality of life and family functioning. *Child participation*: measured using the Young Children’s Participation and Environment Measure (YC-PEM) [32]. The YC-PEM is a caregiver-completed measure that investigates the participation of children aged 0–5 in activities across home and the community. Scores are categorised into frequency, involvement and desire for change. The tool will be adapted and validated for use in this Rwandan population and setting.

Secondary effectiveness outcomes are:*Caregiver knowledge and confidence*: measured using an adapted version of the World Health Organization pre- and post-Parent Skills Training Test for Caregivers [33].*Caregiver psychological distress*: assessed via the Self-Reporting Questionnaire (SRQ) [34].*Caregiver experience of disability-related stigma*: measured using the Affiliate Stigma Scale [35].*Caregiver economic activity*: measured using a time-use survey from the Living Standards Measurement Survey [36].*Child mortality*: confirmed by caregiver report, community health worker or electronic medical records. Recorded at endline only.*Childhood hospital admission due to illness*: hospitalisations (defined as admission of one or more nights) in the past 12 months on caregiver report. Recorded at endline only.*Child development and function*: measured via the development-for-age Z-scores (DAZ) on the Global Scales of Early Development (age 0–3 years) [37], the Malawi Development Assessment Tool (age > 3 years) [30], and the Pediatric Evaluation of Disability Inventory - Computer Adaptive Test (PEDI-CAT) [38].*Child growth and nutritional status*: defined as weight-for-age (underweight), height-for-age (stunting), based on World Health Organization Growth Standards [39].

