### Sample size

The primary analysis will be conducted amongst all children at risk of developmental disabilities and their caregivers. Secondary analysis will be conducted for the sub-population of children with developmental disabilities. Sample size calculations are based on the primary effectiveness outcomes amongst the sub-population of children with developmental disabilities, as this is the population for which data were available and is an important secondary analysis population. As a result, the trial will be powered to detect smaller intervention effects for the primary analysis population of all at risk children. We assume 10 clusters per trial arm with 35 children with developmental disabilities per cluster, for a total of 700 children with development disabilities overall, of whom 20% will not consent to participate in the evaluation or will be lost to follow-up. This results in a total of 560 children with developmental disabilities with outcome data (280 in each trial arm, 28 per cluster). Previously published data from a Ugandan cohort of children (< 3 years) with developmental disabilities suggest a mean family health-related quality of life score (PedsQL) of 60 amongst care as usual families (standard deviation 20) [28]. Data from Brazil suggest a mean YC-PEM home participation frequency raw score of 59 (standard deviation 7.5) and a mean YC-PEM home participation involvement raw score of 43 (standard deviation 7.5) in those receiving standard care [42]. Based on these values, Table 2 indicates detectable differences for family health-related quality of life and child participation among children with developmental disabilities, with 80% power and 5% significance level, for a range of intra-cluster correlation coefficient (ICC) scenarios. Detectable differences are shown as absolute difference, relative difference and as Cohen’s effect size.

**Table 2 Tab2:** Detectable differences in family health-related quality of life and child participation primary outcomes

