### Data analysis

The trial will adopt a superiority design, evaluating whether the PDC/Baby Ubuntu intervention is superior to enhanced usual care in improving primary and secondary outcomes. Analyses will follow intention-to-treat principles. Clusters will be analysed according to their original randomisation, regardless of coverage or other variables.

The full analysis set will consist of all randomised subjects analysed according to the study arm to which they were assigned. The primary analysis will focus on all children at risk of developmental disabilities and their caregivers, comparing those receiving the PDC/Baby Ubuntu programme to the control group. The secondary analysis will compare children with developmental disabilities and their caregivers who received Baby Ubuntu to children with developmental disabilities in the control group. Superiority will be demonstrated if there are statistically significant improvements in the intervention arm versus the control arm for the prespecified outcomes.

Because of the relatively small number of clusters (n ≤ 20), cluster-level analyses will be used to assess the overall effect of the intervention. Specifically, in crude analyses, cluster-level means for each outcome measure will be generated and compared using t-tests. Adjustment for district and cluster size will be done using the two-stage approach described by Hayes and Moulton [43].

In further prespecified exploratory analyses, we will also analyse data at the individual level using generalised linear models (with an appropriate link function depending on the type of data) with random effects to allow for clustering of individuals. As this is not a confirmatory study, we do not plan any formal adjustment for multiple testing. Missing data will be handled using complete case analysis as the primary approach. Multiple imputation methods may also be used as a sensitivity analysis if substantial missing data exists (> 10% missing).

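### The disability sub-population is defined by an endline developmental score that is also a trial outcome, so its membership can depend on arm if the programme changes development

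*Protocol article*

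**What the plan says.** The Baseline data section gives two classification times. It first states "Disability status at baseline will be determined using the Malawi Developmental Assessment Tool (MDAT"). At the end of the same paragraph it sets the cut for moderate to severe developmental disability at a DAZ below −2 "on endline assessment when children are older and diagnosis are more reliable". No other section gives a different DAZ cut-off or time point.

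Randomisation follows the baseline assessment (Randomisation), and endline (T1) is 12 months after randomisation (Participant timeline).

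Under Effectiveness outcomes, child development and function is a secondary outcome "measured via the development-for-age Z-scores (DAZ) on the Global Scales of Early Development" at age 0–3 years, and on the MDAT above that age. Data analysis describes a superiority design "evaluating whether the PDC/Baby Ubuntu intervention is superior to enhanced usual care in improving primary and secondary outcomes".

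The Sample size section names children with developmental disabilities as the secondary analysis population and adds: "Sample size calculations are based on the primary effectiveness outcomes amongst the sub-population of children with developmental disabilities". Data analysis then compares two groups that are not defined alike. The intervention side is children with disabilities who actually received Baby Ubuntu. The control side is all children with disabilities. Table 1 schedules the developmental assessment (MDAT/GSED) at both T0 and T1.

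**The concern.** A sub-population compared between randomised arms should be fixed by information that treatment cannot alter. Here the only numerical definition of disability uses a score taken a year after allocation, and the trial tests whether the programme improves that score. If it does, a child lifted above −2 drops out of the intervention side, while a comparable control child remains. The children left on the intervention side would have scored lower on development without the programme, and probably lower on anything correlated with development.

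The resulting contrast is not the effect of the programme in any population that could be identified at entry. What is at stake is the secondary analysis, which the protocol calls important and on which Table 2 and the recruitment target of about 1,400 are built.

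The condition of having received Baby Ubuntu, applied to one arm only, is a second selection after randomisation. Its direction is unknown.

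**Working it through.** **The plan's own figures.** Inputs from Sample size and Table 2: 10 clusters per arm, 28 analysed children per cluster, SD 20 (PedsQL) or 7.5 (YC-PEM), 80% power, 5% significance taken as two-sided.

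Detectable difference = SD × (1.96 + 0.84) × √[2 × (1 + 27 × ICC) / (28 × 9)], with one cluster per arm removed as a small-sample correction.

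| ICC | PedsQL | YC-PEM |
|---|---|---|
| 0.01 | 5.63 | 2.11 |
| 0.05 | 7.65 | 2.87 |
| 0.1 | 9.60 | 3.60 |

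These match Table 2 (5.6, 7.7, 9.6 and 2.1, 2.9, 3.6). The counts agree too: 20 × 35 = 700; 700 × 0.8 = 560, or 28 per cluster; 700 / 0.5 = 1,400. The sample size arithmetic is sound.

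**Assumptions for the selection effect.** The article gives neither an expected DAZ gain nor a DAZ–PedsQL correlation, so these are mine:
- DAZ without the programme is normal with SD 1.5, and half of children lie below −2. The half is the article's estimate of the share with a disability.
- The mean DAZ gain is 0.3, which is 0.3 / 1.5 = 0.2 SD.
- PedsQL (SD 20) has correlation r = 0.3 to 0.5 with the DAZ the child would have had without the programme.

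**Step 1, who is selected.** Control share = 0.50. Intervention share = Φ(−0.2) = 0.42. If half of the 1,400 are in each arm and 80% are followed, there are 560 per arm, giving about 280 against 236 children.

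**Step 2, how they differ.** Mean untreated DAZ among those selected, in SD units:
- Control: −φ(0)/0.5 = −0.798.
- Intervention: −φ(0.2)/Φ(−0.2) = −0.929.
- Difference: −0.132 SD.

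**Step 3, no true PedsQL effect.** Contrast = 20 × r × (−0.132) = −0.79 at r = 0.3 and −1.32 at r = 0.5. At ICC 0.1 the two-sided error rate is about 5.6% to 6.7% instead of 5%.

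**Step 4, true mean PedsQL effect of 9.6**, the planned detectable difference at ICC 0.1.
- *Same effect in every child:* 9.6 − 0.79 = 8.8 and 9.6 − 1.32 = 8.3, which is 8% to 14% low.
- *DAZ gain of 0.6 in a random half, PedsQL gain independent of it:* the share below −2 is (Φ(−0.4) + 0.5)/2 = 0.42 and the latent difference is −0.111 SD. The estimates are 9.6 − 0.66 = 8.9 and 9.6 − 1.11 = 8.5, about 7% to 12% low.
- *DAZ gain of 0.6 and PedsQL gain of 19.2 in the same half, none in the rest:* responders make up 0.345/(0.345 + 0.5) = 0.408 of those selected. The estimates are 19.2 × 0.408 − 0.66 = 7.2 and 19.2 × 0.408 − 1.11 = 6.7, which is 25% to 30% low.

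**Step 5, precision.** With 23.6 rather than 28 children per intervention cluster, the detectable difference at ICC 0.1 moves from 9.60 to 9.71. The problem is bias, not loss of power.

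**Step 6, no DAZ gain.** The two shares are equal and the bias by this route is zero.

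**The case against.** The primary analysis includes all at-risk children by assigned arm and never uses the endline cut. The primary hypothesis concerns quality of life and participation; development is a secondary outcome with no stated expected gain. So a reader might infer that the sub-population necessarily differs by arm, or that the main result is compromised. Neither follows from the text.

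The endline choice also has a stated reason. Children are enrolled from birth, when classification is less certain. Baseline misclassification has a cost: if, say, 25% of a baseline-defined group were misclassified and gained nothing, a true 9.6 would appear as 0.75 × 9.6 = 7.2. That stands as a real trade-off. But error made before allocation is equal between arms in expectation, whereas selection at endline is not.

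The link to the secondary analysis is partly inferred. The endline sentence defines moderate to severe disability, while Sample size and Data analysis speak of developmental disabilities without that qualifier. It is the likely reading, since no other cut is given.

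Three further inferences are tempting but not supported:
- *The planned severity subgroup is affected.* The article does not say when severity is measured.
- *The endline cut mixes two instruments.* The DAZ in Baseline data is described only from the MDAT scoring application, and the age split belongs to outcome measurement. If the split did govern classification, it would apply at T0 as well.
- *Deaths and losses cannot be classified.* For PedsQL and YC-PEM these children generally have no endline value and leave the complete-case analysis under either definition.

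**Conclusion.** The concern holds in conditional form. The paragraph gives two classification times without reconciling them, and the one carrying the cut-off is a post-randomisation variable that the trial tests for improvement. If the programme changes DAZ, the secondary disability analysis compares differently selected groups, generally to the programme's disadvantage. If DAZ does not move, this route gives no bias.

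Under the stated assumptions the distortion is moderate: −0.8 to −1.3 PedsQL points under no effect, and a true 9.6 underestimated by about 7–14%. The 25–30% figure should not be read as the expected size, because it needs the DAZ and PedsQL gains to fall in exactly the same half of children. The primary analysis and the Table 2 arithmetic stand.

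**What to change.** Reconcile the two sentences in Baseline data and define the disability sub-population in both arms by baseline (T0) DAZ below −2. In Data analysis, drop the condition of having received Baby Ubuntu and analyse this sub-population by assigned arm whatever the attendance. Changing the DAZ time point alone would leave that one-sided selection in place. Keep endline DAZ below −2 as an outcome and as a descriptive sensitivity analysis. Base any severity subgroup on baseline data as well.

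The cost is wording: T0 developmental scores are already scheduled, and the article states that no data had been analysed at submission. The downside is more misclassification among the youngest children, equal between arms in expectation, which may dilute the subgroup effect. Table 2 carries over only if the assumed 50% share with disability also holds at T0, which the baseline data can show.
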